### 2.8. Data Collection

Data collection will occur at five timeframes: T-0, during recruitment before randomization; T-1, on abortion day before discharge (normally 2 h post-abortion procedure); T-2, during women’s post-abortion exam visit, normally 2 weeks post-abortion; T-3, 6 weeks post-abortion; and T-4, post completion of all follow-ups of all participants. See Table 3 for detailed information on data collection, including What, Who, When, Where, How, and by What data.

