##### Abortion Related Outcomes

Abortion related outcomes will be measured according to women’s gestational weeks at abortion, type of abortion, complications, and follow-up-exam attendance.

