### 2.10. Protocol Modifications

During the conduction of the trial, if we observe a higher-than-expected drop-out rate at the two-weeks post-abortion follow-up, we will increase the sample size from 90 (calculated on a 20% attrition rate) to 110 (calculated on a 35% attrition rate) to achieve precision for the estimation of the effect size. Paper-based questionnaires will be left for women to fill out on their own. However, if participants express being overwhelmed by the amount of information required, we will conduct an interview during which participants could ask clarifying questions. This approach will minimize missing data and enhance the retention rate.

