**Figure 2 ijerph-19-06611-f002:**
[figure not shown]
SPIRIT standard flow diagram.

**Table 1 ijerph-19-06611-t001:** Intervention description according to TIDieR checklist.

TIDieR Item	Intervention Group	Control Group
**1.** **BRIEF NAME**	The START intervention	Standard abortion care
**2.** **WHY**	Based on the Transactional Model of Stress and Coping, the START intervention intends to help women cope with abortion experience by addressing the specific stressors they face in the Chinese context, hence promoting well-being	N/A
**3.** **WHAT-Materials**	Consultation, an information booklet, a WeChat-based public profile page, and a hotline	N/A
**4.** **WHAT-Procedure**	All participants allocated to the intervention group will be offered a 30-min face-to-face consultation. The consultation includes a brief introduction of the public profile page, Q&A, and offering emotional support and information on available coping resources. A printed information booklet will be provided during the consultation. Meanwhile, by scan the QR code, participants will be endowed with unlimited access to the public profile page till the closure of the project. A hotline will also be offered.	(1) prior abortion consultation on informed choice of pregnancy; (2) abortion preparation education on abortion practice, and steps involved; (3) a brief discharge education session on warning signs of potential complications and post-abortion contraception; and (4) a regular 2-week post-abortion appointment to determine the completion of the abortion.
**5.** **WHO PROVIDED**	The consultation, information booklet, and managing the public profile page will be carry out by the primary researcher who is a qualified abortion counsellor. Hotline will be answered by a registered nurse who has more than 10 years clinical experience in abortion care.	Prior abortion consultation and post-abortion exam-by doctors Abortion preparation and discharge education-by nurses
**6.** **HOW**	Consultation (face to face) Information booklet (hard copy) Public profile page (internet) Hotline (telephone)	Face to face
**7.** **WHERE**	Consultation (the consultation room) Information booklet (the consultation room) Public profile page (WeChat based) Hotline (telephone-base)	Health centre facilities

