**8.** **WHEN and HOW MUCH**	Consultation (after women made their abortion appointment, 30 min) Information booklet (during the consultation, one copy to take home) Public profile page (from the consultation, unlimited access until the closure of the project) Hotline (from the consultation, available during workhours)	Prior abortion consultation—at women’s first appointment (10–20 min); Abortion preparation education—after women made their abortion appointment (5–10 min); post-abortion education—before women are discharged (10 min); The post-abortion exam—2 weeks after abortion
**9.** **TAILORING**	Participants in the intervention group will receive the same intervention	N/A
**10.** **MODIFI-CATION**	Cannot be reported until the study is complete	N/A
**11.** **HOW WELL**	The research nurse and reception nurses involved in the trial will be trained initially. A researcher logbook will be kept recording intervention delivery of each participant. Adherence to the intervention will be assessed by participants self-reported usage info collected during follow-ups	N/A
**12.** **ACTUAL**	Cannot be reported until the study is complete	N/A

Abbreviations: Q&A: questions and answers; N/A: not applicable.

**Table 2 ijerph-19-06611-t002:** Content of the information booklet and platform.

Categories	Themes	Example Items
Abortion	Facts about abortion	General information about abortion Pregnancy calculation and ectopic pregnancy Abortion practice in Beijing
	Different types of abortion	Medical abortion and steps involved Aspiration/surgical abortion and steps involved Features of aspiration abortion and medical abortion
	Q&A	What is your legal position, e.g., gestation age limits; no need for husbands’ or partners’ permission; and Nation ID required etc. How much does abortion cost? Does abortion hurt and what is a painless induced abortion? What will you experience during an abortion? How could you know your abortion is complete? Will an abortion cause infertility? How will you feel if you have an abortion
	Aftercare and follow-up examination	Follow-up examination and why it is necessary Symptoms requiring contacting your health provider, going to local emergency room, or calling 120 for Emergency Health Aid.
Intimate Relationship	A healthy relationship	Important characteristics of a healthy relationship Rights and responsibilities in a relationship Equality in intimate relationships

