**Effectiveness outcomes**				
Depression	T-0, -1, -2, -3	Primary researcher (T0, 3) and nurse coordinator (T-1, -2); at clinic facilities; face to face (T-0, -1, -2) and by telephone (T-3)	SMD-A	Descriptive statistics *t*-test/Mann–Whitney U test comparing baseline to T-3 *t*-test/Mann–Whitney U test comparing differences between groups at T-3 Linear regression measuring change over time
Perceived support	T-0, -1, -2, -3	As above	MOS-SSS	As above
Intimate relationship	T-0, -1, -2, -3	As above	CSI-4	As above
Coping behaviours	T-0, -2, -3	As above	CBCI	Descriptive statistics *t*-test/Mann–Whitney U test comparing baseline to T-3 of each coping style *t*-test/Mann–Whitney U test comparing differences between groups of each coping style at T-2 and T-3
Self-efficacy	T-0, -2, -3	As above	GSE-10	Descriptive statistics *t*-test/Mann–Whitney U test comparing baseline to T-3 *t*-test/Mann–Whitney U test comparing differences between groups at T-2 and T-3
Post-abortion growth	T-2, -3	As above	PTGI-SF	Descriptive statistics *t*-test/Mann–Whitney U test comparing T-2 to T-3 *t*-test/Mann–Whitney U test comparing differences between groups at T-2 and T-3
Abortion outcomes	T-3	As above	Self-design questions	Descriptive statistics Chi Square test comparing differences between groups at T-3

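### T-2 is collected at the post-abortion exam with no stated route for women who miss it, although attendance is itself a compared outcome, so the secondary T-2 comparisons are open to selection bias

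*Protocol article*

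**What the plan says.** Section 2.8 defines T-2 by a clinic event, the "post-abortion exam visit, normally 2 weeks post-abortion". Table 3 gives the mode for the effectiveness outcomes as "face to face (T-0, -1, -2) and by telephone (T-3"), with T-2 in the hands of the nurse coordinator at the clinic. Neither place describes another way of obtaining T-2 data.

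The same visit appears in three other roles:

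- **As an outcome.** The abortion-related outcomes in section 2.4.3 include "type of abortion, complications, and follow-up-exam attendance". Table 3 compares this group of outcomes between arms by chi-square.
- **As intervention content.** Table 2 lists, for the START booklet and platform, "Follow-up examination and why it is necessary".
- **As standard care.** Table 1 gives control women "a regular 2-week post-abortion appointment to determine the completion of the abortion".

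Table 3 plans a *t*- or Mann–Whitney "test comparing differences between groups of each coping style at T-2 and T-3", and the same for self-efficacy and post-abortion growth. Growth is measured at T-2 and T-3 only and is also compared between those two times. Depression, perceived support and relationship satisfaction are measured at T-2 as well and enter a linear regression on change over time.

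Section 2.10 raises recruitment from 90 to 110 "if we observe a higher-than-expected drop-out rate at the two-weeks post-abortion follow-up".

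**The concern.** Randomisation makes the two arms comparable as randomised. It does not make women who attend a later visit comparable across arms. Here the visit at which T-2 data are taken comes after randomisation, is encouraged by material that only the START arm receives, and is tested as an outcome. If START changes who comes back, and women who come back differ from those who do not in coping, self-efficacy or growth, a T-2 test among attenders can show a difference that START did not cause, or hide one that it did. Growth is the most exposed outcome, because it has no baseline value to adjust for.

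There is a knock-on question for the enlargement rule. Section 2.10 acts on drop-out at two weeks, while section 2.9 judges retention at six weeks, when Table 3 uses the telephone. A woman who skips the exam but answers the six-week call is retained under section 2.9. Under section 2.10 she might be read as a drop-out.

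**Working it through.** **The plan's own figures.** Taking the 72 evaluable women of section 2.5 as given, 72 / (1 − 0.20) = 90, as stated. For section 2.10, 72 / (1 − 0.35) = 110.8, against the stated 110. The enlargement replaces lost numbers. It does not change which women supply T-2 data, so it leaves any selection in place.

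**Which analyses depend on the exam (Table 3)**

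| Analysis | Uses T-2? |
|---|---|
| Depression, between groups at T-3 (primary outcome) | No; T-3 is by telephone |
| Coping, self-efficacy, growth, between groups at T-2 | Yes |
| Growth, T-2 to T-3 | Yes |
| Depression, support, relationship: regression over time | Yes, for the T-2 points |

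**Size, first illustration.** The article gives no attendance by arm and no difference between attenders and non-attenders. The following inputs are assumptions: attendance 80% with START and 60% without, a gap δ between attenders and non-attenders that is the same in both arms, and no true effect. With attendance p, the attender mean equals the overall mean plus (1 − p) × δ.

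- START: 0.20 × δ. Control: 0.40 × δ.
- Spurious difference, START minus control: −0.20 × δ.
- δ = 0.3 SD gives 0.06 SD in absolute size, δ = 0.5 gives 0.10, and δ = 0.8 gives 0.16.

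The sign depends on who attends. If attenders cope better, the bias runs against START; if they cope worse, it favours START.

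With 45 per arm, 36 and 27 women attend. The standard error is √(1/36 + 1/27) ≈ 0.25 SD, so a 0.10 SD shift raises the type I error from 5% to about 7% (5.6% to 9.6% over the range of δ).

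**Size, second illustration.** A bivariate-normal selection model was also run, in which the mean among attenders is ρ × φ(z) / p, with z the normal cut-off for attendance p and ρ the assumed correlation between attendance and outcome. For ρ from 0.2 to 0.5, 45 per arm and no true effect:

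| Attendance, control v START | Spurious difference (SD, absolute) | Type I error |
|---|---|---|
| 80% v 90% | 0.03 to 0.08 | 5.2% to 6.3% |
| 70% v 90% | 0.06 to 0.15 | 5.7% to 9.7% |
| 65% v 95% | 0.09 to 0.23 | 6.7% to 16.1% |

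If attendance is equal (80% or 65%) but selection differs by arm (ρ of 0.3 v 0, or 0.3 v −0.3), the difference is 0.11 to 0.34 SD and the type I error 7% to 26%. If both attendance and selection are the same in the two arms, the bias is zero.

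**The case against.** The strongest reply is that differential selection is assumed, not shown. Both arms have the same routine two-week appointment. The encouragement is one example item in a long content table. Listing attendance as an outcome does not prove that START aims to change it, since the same list holds gestational weeks and type of abortion. This stands: a reader might infer that the T-2 tests will compare differently selected women, but the documents support only that they may.

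Second, the abstract says that all participants are followed up at two weeks, and a condensed article may leave the chasing of missed visits to the full protocol. So it cannot be said that non-attenders will certainly have no T-2 data. What stands is that sections 2.8 and Table 3 do more than stay silent: they name the exam as the occasion and in-person contact as the mode, and they reserve the telephone for T-3. The paper questionnaires in section 2.10 concern self-completion versus interview and are not said to reach women who miss the exam.

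Third, section 2.10 does not define drop-out as a missed exam. A reader might infer that the trigger counts missed exams, but the wording only permits that reading. Were it to fire that way, the direct result would be 20 more women, not bias.

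Fourth, this is a feasibility trial with preliminary efficacy testing, and loss to follow-up and missing data are themselves feasibility outcomes. That limits the weight of the point but does not remove it, because the T-2 tests are planned.

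**Conclusion.** The point holds as a structural risk to secondary analyses. As written, T-2 data depend on a post-randomisation behaviour that START material encourages and that the trial compares between arms. Bias requires that START changes who attends and that attendance is related to the outcome. The documents show neither, and the direction is unknown. Under the 80% v 60% assumption the size is 0.06 to 0.16 SD. Other assumptions give anything from zero to 0.34 SD.

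Two stronger readings should be resisted. The illustration should not be expressed as a share of the 0.39 in section 2.5: that effect is for depression, and no planning effect is given for coping, self-efficacy or growth. Nor is the primary comparison undermined, since the between-group depression test is at T-3 by telephone; only the T-2 depression point in the regression is exposed. This is an inexpensive improvement worth making, not a defect that invalidates the trial.

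**What to change.** In section 2.8 and Table 3, define T-2 as two weeks post-abortion for every randomised woman. Collect it at the exam if she attends and otherwise by telephone within a set window. The telephone is already used at T-3, and the change would bring the text into line with the abstract. Keep exam attendance as a separate outcome that does not determine whether T-2 data exist.

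In section 2.10, state that the trigger counts women who cannot be reached at two weeks, not women who missed the exam.

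The cost is the calls and a wording change. At the illustrative attendance, 9 START and 18 control women would need a call, 27 of 90. The collection mode at T-2 would then be mixed and possibly unbalanced: with 20% v 40% answering by telephone, a mode effect of m SD would leave a difference of 0.20 × m. The mode should therefore be recorded for each woman and reported by arm.

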### 2.9. Data Analysis

Participant characteristics, feasibility outcomes, and quantitative acceptability outcome data will be summarized with descriptive statistics, including frequency counts and percentages (categorical variables) and mean with 95% confidence intervals (CIs) or standard deviation (continuous variables). Intervention feasibility and acceptability will be assessed against the following criteria: eligibility: ≥60% of patients screened will be eligible; recruitment: ≥80% of eligible participants will agree to participate; protocol fidelity: ≥90% of patients randomized to each group will receive the allocated intervention; retention: <20% of patients will be lost at 6 weeks after abortion; and missing data: <20% of data will be missing. Between-group differences of participant characteristics, baseline data, and effectiveness outcomes will be detected using Statistical Package for the Social Sciences (SPSS)^®^ version 23 [41]. Specifically, Chi square tests will be used for categorical/dichotomous variables, and *t*-tests or Mann–Whitney U tests for continuous variables (depending on normality). To capture changes in the effect outcomes over time, a general linear regression analysis will be performed. See Table 3 for the specific analysis approaches.

For qualitative data, audiotapes of telephone interviews will be transcribed and de-identified by the primary researcher. Transcripts and notes will be analyzed using the deductive approach of content analysis [42]. First, a structured analysis matrix will be developed based on the aims of the study and the TFA of Health Care Intervention. Then the primary researcher and nurse coordinator will independently review all de-identified data, and content fit the matrix. They will work together to group similar content within the matrix boundaries as categories, and then main categories. After abstraction of each category, the primary researcher and nurse coordinator will make a joint decision on how to model and report the results. Any discrepancies along the process will be discussed with a third reviewer until an agreement is reached. To preserve the original meaning of women’s statements, the data analysis process will be conducted using Chinese. Development of the analysis matrix and reporting process will use Chinese and English to reduce potential bias and build a shared vision among the research team.

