### 2.5. Sample Size

A formal sample-size calculation is not necessary for research objectives 1 and 2 [20]. For objective 3, G*Power software was used to determine reasonable sample size for the estimation of differences between intervention and control groups. The effect size on depression reported by similar interventions ranged from 0.39 to 1.06 [37,38,39]. G*power indicated a total of 72 participants will be required to detect a 0.39 effect size for depression, two tailed, with alpha at 0.05 and power at 90%. Anticipating a 20% attrition rate, recruitment was set at 90 (45 women per group).

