## 3. Discussion

We propose a two-armed randomized trial among Chinese women undergoing abortion, to assess the feasibility, acceptability, and potential effects of the START intervention. To our knowledge, this study will be the first trial to address Chinese abortion patients’ psychological wellbeing by providing a comprehensive supportive intervention based on the Transactional Model of Stress and Coping [19]. This innovative intervention contains different active components that will be delivered using different methods. Findings from this trial will allow us to evaluate the feasibility and acceptability of the intervention, which will inform intervention refinement [17]. The findings will also help to identify potential barriers and facilitators for implementing the intervention in the Chinese context [43]. As the preliminary effectiveness and effect of the intervention will also be described, the study could have important implications for relevant policymakers, practitioners, researchers, or other stakeholders [44].

We are employing a rigorous study design to ensure the internal and external validity of findings. This trial responds to the call for well-designed, rigorously conducted scientific research in abortion care in developing countries [1]. Randomization and statistical analysis adjusted for any difference in baseline characteristics between groups will protect against selection bias, and ultimately warrant internal validity [45]. The study will be performed under real-world clinical practice conditions, which will enhance the external validity and generalizability of results. All instruments used in this study have been validated in the Chinese population, which will also enhance the reliability of findings.

A further strength is that we have adopted a series of appropriate guidelines to ensure the normalization, transparency, and replication of the study. The TIDieR checklist has been used to describe the intervention [23]. Application of the CONSORT statements [20,21] and the SPIRIT 2013 Checklist [22] have been followed.

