## 4. Conclusions

This paper proposes a protocol of a clinical trial to assess the feasibility, acceptability, and potential effects of a comprehensive supportive intervention that was developed to address the psychological health of Chinese women undergoing an abortion. Results will be used to assist intervention refinement and direct a future full-powered trial. Practical experience will be gained throughout the clinical trial, which would also provide evidence for further implementation of the intervention.

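### An undefined normality check picks the between-arm test for each scale, and no listed analysis is named as the source of the between-arm effect and its confidence interval

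*Protocol article*

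**What the plan says.** **The rule.** Section 2.9 (Data Analysis) compares continuous variables between arms by t-tests or "Mann–Whitney U tests for continuous variables (depending on normality"). It names no normality test or threshold, and does not say whether the check is made per arm, pooled or per visit.

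**Table 3, effectiveness outcomes:**
- Depression (primary): descriptive statistics, then a t-test or "Mann–Whitney U test comparing differences between groups at T-3 Linear regression measuring change over time". Perceived support and intimate relationship follow the same plan.
- Coping, self-efficacy and post-abortion growth: descriptive statistics and a t-test or Mann–Whitney test between arms at both T-2 and T-3. No regression is listed.

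**The regression.** Section 2.9 adds: "To capture changes in the effect outcomes over time, a general linear regression analysis will be performed". This does not depend on normality. Table 3 is cited for the specific approaches.

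**The stated aims.** Section 2.5 used power software "to determine reasonable sample size for the estimation of differences between intervention and control groups". Section 2.10 would raise recruitment from 90 to 110 "to achieve precision for the estimation of the effect size". Section 3 (Discussion) relies on "statistical analysis adjusted for any difference in baseline characteristics between groups". Section 4 says: "Results will be used to assist intervention refinement and direct a future full-powered trial".

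**The concern.** A t-test concerns a difference in means. A Mann–Whitney test concerns the ordering of scores between the arms, and as named here it brings no mean difference, standardised effect or interval. When the observed data choose between them, the quantity being compared is not fixed in advance. Neither test uses the T-0 score, so neither delivers the adjustment that the Discussion relies on.

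This matters more here than in a trial planned only to reject a null hypothesis. The trial is small and says that it is sized to estimate a difference and to guide a larger trial. A reader planning that trial needs a between-arm estimate, its interval and the SD for each scale. The protocol does not say which listed analysis provides the estimate and interval. A non-significant rank test reported alone would not show how large an effect remains possible.

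**Working it through.** **1. What each scale has between arms in Table 3**

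| Scale | Switched test between arms | Regression listed | T-0 score |
|---|---|---|---|
| Depression (primary) | T-3 | yes | yes |
| Perceived support | T-3 | yes | yes |
| Intimate relationship | T-3 | yes | yes |
| Coping | T-2 and T-3 | no | yes |
| Self-efficacy | T-2 and T-3 | no | yes |
| Post-abortion growth | T-2 and T-3 | no | no |

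In the first three rows the regression could supply a between-arm estimate, but its stated purpose is change over time, and no group or group-by-time term is given. The only entry described as a comparison between groups is the switched test. In the last three rows that test is the only between-arm analysis listed. Only there can the test differ between T-2 and T-3 of one scale.

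The wording in Section 2.9 about means with 95% confidence intervals covers characteristics, feasibility and acceptability. It does not mention the effectiveness comparisons.

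**2. The plan's own numbers**

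- Attrition: 72/0.80 = 90, as stated. 72/0.65 = 110.8, against 110 stated.
- Completers per arm at 1:1 allocation: 72/2 = 36.
- The 72 itself does not reproduce for two independent groups. 2 × (1.960 + 1.282)²/0.39² = 138.2, so 139 per arm or 278 in total. A paired or one-sample t-test gives 71.03, so 72. That is a separate matter; here 36 per arm serves only as the planned number of completers.

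**3. The interval that the plan does not ask for**

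For an observed standardised difference of 0.39 with 36 per arm:

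SE = √(2/36 + 0.39²/(2 × 72)) = √(0.05556 + 0.00106) = 0.238

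Half-width = 1.96 × 0.238 = 0.466, so the 95% interval is about −0.08 to 0.86. This width comes from the sample size, not from the choice of test. It shows what a bare p-value would leave unseen.

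**4. How often the switch might matter**

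The documents give no mean, SD or normality criterion, so this step rests on assumptions: negative-binomial scores capped at 27 (the PHQ-9 maximum in Section 2.4.3), 36 per arm, a mean lower by 0.39 SD in one arm with the SD unchanged, and Shapiro-Wilk at 5% in either arm as the check.

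| Assumed mean, SD | Mann–Whitney selected | Tests disagree at 0.05 | Power, t-test | Power, Mann–Whitney |
|---|---|---|---|---|
| 13, 5.5 | 52% | 8% | – | – |
| 10, 5.5 | 87% | 10% | 40% | 46% |
| 7, 5 | 99.7% | 16% | 39% | 53% |
| 5, 4.5 | 100% | 26% | 41% | 66% |

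Other score shapes or another normality check would change these figures. Table 3 names SMD-A rather than PHQ-9 as the depression measure, so even the 0–27 range needs reconciling.

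**The case against.** A reader might infer that the depression result could end as a rank p-value with no effect size, so that the next trial could not be sized. The documents do not support that. The depression cell of Table 3 also lists descriptive statistics and a linear regression, and Section 2.9 plans the regression whatever the normality check shows. Arm means and SDs, if reported, would let anyone compute a difference and an interval. This part of the objection stands for depression, perceived support and intimate relationship.

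A reader might also infer that the depression test can change between T-2 and T-3. It cannot on Table 3, which lists a between-arm test for depression at T-3 only.

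Other points against are fair. A rank test for a skewed, bounded score is conventional. Objective 3 is preliminary. An article may leave the normality criterion and the effect measure to a fuller plan. The simulated percentages rest on assumptions, and disagreement between two tests at low power is not by itself bias or an inflated type I error; neither has been shown.

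These points do not remove the core. The data-dependent choice is stated in the protocol, not merely left open. The regression has no stated treatment term. On Table 3, coping, self-efficacy and growth have no other between-arm analysis; the general sentence in Section 2.9 might be read to cover them, but that section sends the reader to Table 3 for specifics. Summary statistics from which a reader could build an estimate are not a planned estimate.

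**Conclusion.** The point holds in a limited form. An undefined check, made after the data are seen, chooses between two unadjusted tests that address different quantities. No listed analysis is designated to give the between-arm effect with its interval. For three scales an effect size is probably recoverable but not assured; for the other three, Table 3 lists only the switched test between arms. This sits badly with the estimation aims in Sections 2.5 and 2.10 and with the baseline adjustment in the Discussion.

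That much follows from the text alone. How often the test would switch (about half to all trials) and how often the tests would disagree (8% to 26%) hold only under the assumed distributions and Shapiro-Wilk rule. The change is worth making before analysis because it is nearly free. It is not a flaw that invalidates the trial.

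**What to change.** In Section 2.9 and Table 3, remove the dependence on normality and fix one between-arm analysis for every scale:

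- Estimate the mean difference from a linear model with a treatment term. Adjust for the T-0 score where one exists; leave post-abortion growth unadjusted, since it is first measured at T-2.
- Report it with a 95% confidence interval, robust or bootstrap if scores are skewed, and with the SD.
- Name this as the analysis that supplies the between-arm effect, with T-3 depression as primary.
- Keep Mann–Whitney as a labelled sensitivity analysis.

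**Cost.** Wording only. The T-0 scores are already collected, and no extra participants are needed.

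**Downside.** The mean difference can be less powerful than the rank test when scores are very skewed. In the assumed scenarios the unadjusted loss was 6 percentage points at mean 10 (46% against 40%), but 25 at mean 5 (66% against 41%). Part of that gap arises because the assumed arms differ in shape as well as in mean, so the two tests are not measuring the same thing. Baseline adjustment, not included in those figures, should recover some power if the T-0 score predicts the outcome.
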